## Background

Total knee replacement (TKR) is a common and successful procedure, with over 1 million TKRs occurring annually in OECD countries [1]. TKR is regularly performed using a tourniquet, with usage in 37–93% of surgeries [2, 3]. However, tourniquet use during TKR is debated due to evidence questioning the advantages, and the possibility of increased complications [4, 5].

A thigh tourniquet compresses the leg and restricts distal blood flow which is intended to reduce intra-operative blood loss at the surgical site. Tourniquet use has been suggested to improve surgical field view, allow cement to bond more effectively [6], and produce shorter operating time which might reduce the risk of infection [4]. A systematic review found tourniquet use reduced intra-operative blood loss (198 ml) and operating time (5 min), but did not affect post-operative blood loss or the possibility of requiring transfusion [4]. Tourniquet use increased the risk of thrombotic events such as deep vein thrombosis (DVT) and pulmonary embolism (PE) (risk ratio (RR) 5.00; 95% CI, 1.31 to 19.10), and non-thrombotic complications such as reoperation, haematoma, or nerve palsy (RR, 2.03; 95% CI, 1.12 to 3.67). Knee range of movement in the first 10 days post-operatively was 10.4 degrees less in the tourniquet group. More recently, Rathod et al. [7] found no difference in cement penetration when a tourniquet was used from incision to arthrotomy closure compared to using a tourniquet only during cementation. Pfitzner et al. [8] found cement mantle thickness was 1.2 mm (*p* = .009) greater in the tourniquet group than non-tourniquet group, and Ledin et al. [9] found no difference in prosthesis migration in tourniquet versus non-tourniquet TKR. Several investigators have reported higher post-operative pain when a tourniquet was used compared to no tourniquet [9–11].

Quadriceps function influences post-operative physical performance, functional ability and rehabilitation following TKR [12, 13]. Quadriceps dysfunction following TKR can be immediate, profound and persist for years after surgery, resulting in substantial functional deficits [14]. Mizner et al. [15] found quadriceps strength was 62% less than pre-operative values when measured four weeks after TKR.

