### Surgery

One of 12 surgeons will complete each TKR, with training registrars operating under direct supervision. Prosthesis type and whether to use navigated or non-navigated TKR is at the surgeon’s discretion, which will be decided upon prior to knowledge of the participant’s group allocation. A medial parapatella approach and no drain will be used for all participants.

The tourniquet group will have a tourniquet applied with padding. After exsanguination of the operated limb using a rubber tube or esmarch exsanguinator, the tourniquet will be inflated to 100 mmHg above systolic blood pressure or 250 mmHg, whichever is higher. The tourniquet will be deflated immediately prior to wound closure.

All participants receive intravenous Tranexamic Acid (TXA) to reduce peri-operative bleeding. The typical dose is 1 g TXA diluted in 100 ml normal saline infused intravenously at induction. Once the participant is in the recovery room, a second dose of 1 g TXA in 100 ml normal saline is given via infusion pump over 8 h (12.5 ml/hr).

All participants receive DVT prophylaxis commencing six hours after TKR unless contraindicated: clexane 40 mg daily for 14 days. Mechanical DVT prophylaxis via foot pumps will be applied until the patient commences ambulating at least 5 m daily.

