### Post-operative care and rehabilitation

Post-operative care of all participants, irrespective of group allocation will be according to the organisation’s TKR protocols and care pathways. Participants are mobilized day-one post-operatively and participate in a daily rehabilitation program as coordinated by Allied Health staff. Participants are discharged to their usual place of residence once they are medically fit and sufficiently independent with activities of daily living. Participants are sent to inpatient rehabilitation if they are not sufficiently independent to manage at home, which often coincides with living alone. Following discharge from inpatient care, all participants receive ongoing rehabilitation under the direction of Allied Health staff, which is ceased at the discretion of staff and participants. The organisation’s care pathways allow professional discretion regarding the amount and content of rehabilitation completed. Complete standardization of each group’s rehabilitation program is beyond the jurisdiction of the current study and is a potential limitation. Participation in ongoing rehabilitation will be recorded, equivalence between groups assessed and differences will inform data analysis and interpretation.

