### Outcome measures and assessment time points

The primary outcome is the maximum percentage change in isometric quadriceps strength assessed preoperatively and 3 months following TKR. Strength will be measured in Newtons and assessed using a fixed-base electromechanical dynamometer (IsoForceControl EVO2 dynamometer [20]) with the knee stabilised in 60 degrees of flexion. Patient will be seated in a customised chair with a frame that fixes the dynamometer in position. The force plate will be applied adjacent to the malleoli of the ankle. Following 1–2 practices, participants will extend their knee as forcefully as they can for 10 s. The maximum force from three consecutive attempts will be recorded. Fixed-based dynamometer has very good to excellent reliability in people following arthroplasty [21].

Quadriceps strength at day 2 and 5, and 12 months post-operatively are secondary outcomes. Other secondary outcomes include:Post-operative inpatient pain and analgesia requirementsKnee pain intensity on day 2 and 5 post-operatively according to a 0–10 numeric scale (0 = no pain, 10 = extreme pain)Morphine equivalent daily dose [22] (mg, average for first 5 days)Blood loss and replacementIntra-operative blood loss (ml, sucker bottle minus irrigation volume)Transfusion (units)Surgeon satisfaction with intra-operative visual field1–10 numeric scale (1 = completely unsatisfied, 10 = completely satisfied)Operation and anaesthetic time (minutes)Complications during inpatient stayDVT or PEWound complications such as infection, haematoma or breakdown which require a change in management such as antibiotics or reoperationMedical complications (Medical Emergency Team (MET) calls [23] or death)Hospital length of stay (days)Self-reported pain, physical function and quality of life at 3 and 12 monthsKnee Society Score (KSS) [24]Oxford Knee Score (OKS) [25]WOMAC [26]EQ-5D-5 L [27]Revision surgery within 12 monthsCement mantle quality at 12 months [28]Patient satisfaction at 3 and 12 months

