### Adverse events and data safety and monitoring

An adverse event refers to an untoward occurrence during the study, which may or may not be causally related to the intervention [32]. We will collect information relating to adverse events from randomisation until the participant completes the 12 month post-operative assessment.

Serious adverse events (SAE) are those which result in death, are immediately life-threatening, rehospitalisation, result in persistent or significant disability or incapacity, or have important clinical sequelae. Serious adverse events will be reported to the organisation’s Human Research Ethics Committee. All adverse events will be reviewed on a monthly basis by senior surgeons in the organisation’s orthopaedic department. Senior surgeons will consider the likely contribution of tourniquet use towards each complication and recommend to the investigators whether to modify or cease the study based on their findings. The surgeon whose patient had the adverse event will be excluded from the final decision making regarding whether the event is related to tourniquet use. Annual reports of the study’s progress will be sent to the organisation’s Human Research Ethics Committee.

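### The named complications outcome stops at discharge, so post-discharge DVT/PE, treated wound complications and reoperations short of revision are outside the stated between-arm comparison

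*Protocol article*

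**What the plan says.** Under Outcome measures and assessment time points, the protocol article lists the harm outcome as "Complications during inpatient stayDVT or PEWound complications such as infection, haematoma or breakdown which require a change in management". Medical complications (emergency team calls or death) come under the same inpatient label. Table 1 agrees: the Complications row has one mark, in the inpatient column, and none at 3 or 12 months. Revision surgery within 12 months is a separate outcome with its own 12-month mark.

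Four other places bear on this window:

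- **Objectives.** The complications objective includes revision surgery and is not restricted to the hospital stay.
- **Surgery.** Drug prophylaxis is "clexane 40 mg daily for 14 days".
- **Post-operative care and rehabilitation.** "Participants are discharged to their usual place of residence once they are medically fit and sufficiently independent with activities of daily living". Others go elsewhere: "Participants are sent to inpatient rehabilitation if they are not sufficiently independent to manage at home". Whether that period counts as inpatient stay is not stated.
- **Adverse events and data safety and monitoring.** "We will collect information relating to adverse events from randomisation until the participant completes the 12 month post-operative assessment". On their use: "All adverse events will be reviewed on a monthly basis by senior surgeons in the organisation’s orthopaedic department". Serious events also go to the ethics committee. No between-arm comparison of these events is described.

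**The concern.** The Background gives harm as a main reason to question the tourniquet. It says "Tourniquet use increased the risk of thrombotic events such as deep vein thrombosis (DVT) and pulmonary embolism (PE"), with a risk ratio of 5.00 (95% CI 1.31 to 19.10). It also cites a risk ratio of 2.03 for non-thrombotic complications such as reoperation, haematoma or nerve palsy. The outcome that should inform this question has two weaknesses.

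First, it is incomplete. A participant readmitted after discharge with a pulmonary embolism, or with a wound infection needing antibiotics, is recorded as an adverse event but scores as free of complications in the named outcome.

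Second, the observation time is not fixed. It ends when the participant is fit and independent enough to leave, which is a post-randomisation event that treatment may influence. The statistical section analyses categorical outcomes by logistic regression and mentions no allowance for differing observation time. If stays differed between arms, the arm that stayed longer would have more time in which to record an event.

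At stake is whether a reader can take the reported complication comparison as a fair and reasonably full account of harm.

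**Working it through.** **1. The stated windows side by side**

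| Item | Window | Stated use |
|---|---|---|
| DVT/PE, wound and medical complications | Surgery to discharge, variable | Secondary outcome |
| Revision surgery | 12 months | Secondary outcome |
| All adverse events | "from randomisation until the participant completes the 12 month post-operative assessment" | Monthly surgeon review; ethics reporting of serious events |
| Complications objective | No limit stated | – |

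The gap is the set of post-discharge events other than revision. They are collected, but no named outcome compares them. This conclusion needs no arithmetic.

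**2. The plan's own figure.** There is no calculation for complications. The only design figure is the sample size for strength. With d = 0.65, two-sided alpha 0.05 and 80% power, the two-sample t-test needs 38.14, so 39 per arm, as stated. For drop-out, 39 × 1.15 = 44.9, which gives the stated 45 (39/0.85 = 45.9 would give 46). I use 45 per arm below.

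**3. Share of time covered (assumed stay).** No length of stay is given. Day-5 pain is listed under inpatient pain, and the opioid dose averaged over the first 5 days is marked as inpatient in Table 1. A 3-day stay is therefore unlikely, so I take 5 to 10 days.

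- Of the 14-day prophylaxis period: 5/14 = 36%; 10/14 = 71%.
- Of 90 days (about 3 months): 5/90 = 5.6%; 10/90 = 11.1%.

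**4. Share of events covered (assumed timing).** Share of time equals share of events only if the hazard is constant. If the hazard falls as exp(−t/τ), the share of events to day W that occur within a stay of L days is (1 − exp(−L/τ)) / (1 − exp(−W/τ)). For τ = 14, L = 5, W = 14 this is 0.300/0.632 = 47%. Over τ = 7 to 21 days:

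| Stay | Of 14-day events | Of 90-day events |
|---|---|---|
| 5 days | 44% to 59% | 22% to 51% |
| 10 days | 78% to 88% | 38% to 76% |

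**5. Effect of unequal stays (assumed, no true treatment effect).** For rare events, the apparent risk ratio is the ratio of cumulative hazards over the two stays.

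- 5 versus 6 days: 6/5 = 1.20 with constant hazard; 1.13 to 1.17 with decaying hazard.
- 5 versus 7 days: 7/5 = 1.40 with constant hazard; 1.24 to 1.34 with decaying hazard.

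**6. Power for DVT/PE (assumed control risk 1% to 3%, the cited risk ratio of 5.00, n = 45 per arm).** Normal approximation: Φ{[|p1 − p2| − 1.96·√(2p̄(1 − p̄)/n)] / √([p1(1 − p1) + p2(1 − p2)]/n)}. For 2% versus 10%: (0.08 − 1.96 × 0.0501)/0.0494 = −0.37, so power is 36%.

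| Share of events counted | Power |
|---|---|
| All | 20% to 51% |
| Half | 12% to 28% |
| One third | 9% to 20% |

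Expected counts are very small (at 2%, with all events counted: 0.9 versus 4.5), so these powers are rough.

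**The case against.** The strongest reply is that nothing is lost. Adverse events are collected to 12 months, rehospitalisation is classed as serious, and senior surgeons review every event for a tourniquet contribution. By-arm adverse-event tables are commonly left to the full protocol or statistical analysis plan, so their absence from a journal article proves nothing. This stands against a reading that a reader might infer, namely that later events vanish from the trial or will never be compared. The documents do not support that. They do fix the window of the named outcome, in the outcome list and again in Table 1, and an adverse-event table elsewhere would not change it.

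Several other points also stand:

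- Revision to 12 months is compared, so a late wound problem that leads to revision is counted.
- A reader might infer that most of the at-risk period is missed. That is not established. At 10 days the stay covers most of the 14-day period, and events clustered early would raise the share captured.
- A reader might infer that the arms are in fact watched for different lengths of time. The documents report no difference in stay, and clinical staff other than the treating surgeons and theatre staff are blinded. Complications can also lengthen a stay, so longer observation may be a result of events. The bias is possible, not shown.
- The 14-day prophylaxis is not a statement about how long clot risk lasts. It serves here only as a yardstick.
- The Background gives no follow-up window for either risk ratio, so it does not show that these harms arise after discharge.
- Power for DVT/PE is poor under any window.

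None of this explains why an objective without a time limit is measured over a discharge-dependent window when longer data are being collected.

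**Conclusion.** The point holds as a limitation of the named outcome, not of data collection. Outside revision surgery, the stated between-arm comparison of complications ends at discharge. Its length varies with recovery, may vary with treatment, and is unclear for participants sent to inpatient rehabilitation. Post-discharge DVT/PE, treated wound complications, deaths and reoperations short of revision fall outside it.

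The size cannot be computed from the documents. Every percentage and risk ratio in the working beyond the sample-size check rests on assumed stays, event timing or baseline risk, and shows only what range is plausible. A null result on complications would be weak evidence with either window at 45 per arm. What is gained is a count that is equal in follow-up and more complete, which matters for harms reporting and later pooling. This is a worthwhile, inexpensive improvement; it does not touch the primary outcome.

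**What to change.** By a dated, disclosed amendment made before any unblinded analysis:

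- Add a between-arm comparison of DVT/PE, wound complications, reoperation, readmission and death over a fixed window from surgery, to 3 months and again to 12 months.
- Fill it from the adverse-event data already collected, coded to the same definitions for every participant.
- Report the inpatient count as published alongside it, and state whether inpatient rehabilitation belongs to the inpatient stay.
- Add 3- and 12-month marks to the Complications row of Table 1.

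The cost is coding of existing records and the amendment itself; no new visits are needed. Recruitment was planned over four years from October 2014 and the article appeared in December 2018. This would therefore be a late change, and it must be labelled as such. Events treated elsewhere after discharge may be less completely ascertained, and the article does not say how they are found. The longer window does not solve the low power for rare events, so estimates with intervals should carry the interpretation. Nothing here bears on prophylaxis or other clinical care.

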## Methods

### Study design

The study is a single centre, parallel-arm, double-blinded (participant and assessor), randomised trial with 1:1 random allocation. The study schedule is summarized in Table 1.

**Table 1 Tab1:** Study schedule

	Pre-randomisation	Surgery Day 0	Post-surgery				
			Day 2	Day 5	During inpatient stay	3 months	12 months
Enrolment							
Eligibility screen	X						
Informed consent	X						
Randomisation		X					
Interventions							
Tourniquet TKR		X					
No tourniquet TKR		X					
Assessments							
Demographic variables	X						
Quadriceps strength	X		X	X		X	X
Blood loss and replacement		X			X		
Surgeon satisfaction		X					
Operation and anaesthetic time		X					
Tourniquet inflation time		X					
Pain			X	X			
Morphine equivalent daily dose					X		
Complications					X		
Knee Society Score	X					X	
Oxford Knee Score	X					X	X
WOMAC	X					X	X
EQ-5D-5 L	X					X	X
Revision surgery							X
Cement mantle							X

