### Randomisation

People who meet eligibility requirements and provide informed consent will be randomly allocated to either tourniquet or non-tourniquet groups with a 1:1 allocation ratio in blocks of 10. The allocation sequence will be computer generated by the research coordinator prior to trial commencement. Allocation will be concealed until immediately prior to anaesthetic induction, at which time the surgeon will access the allocation code for that participant via an opaque sealed envelope.

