### Blinding

All participants, clinical staff and research staff will be blinded to group allocation, with the exception of the treating surgeon/s and theatre staff.

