Strength measurements will be collected by research assistants, who are trained by a study investigator. The KSS will be completed by the treating surgeon, training registrar or resident. Participants will complete standardised questionnaires in paper-format with assistance offered by a research assistant as required. Cement mantle quality will be determined by a surgeon or research assistant trained by a surgeon. Data for the remaining outcomes will be extracted from the participant’s medical record. Research assistants will enter data into REDCap, the study’s password-protected electronic data collection and management tool hosted by the institution [29].

The study will collect baseline demographic information including age, sex, height, body weight, American Society of Anesthesiologists (ASA) score [30], cognitive function (mini-mental state examination [19]) and medical comorbidities summarized with the Charlson Comorbidity Index [31]. Prosthesis type and the use of navigated or non-navigated procedures will be recorded.

Once participants are enrolled in the study and undergone surgery, every reasonable effort will be made to reassess them for the entire study period. Research assistants will attempt to contact participants a maximum of four times over a three-month period using phone, email or mail before they are considered lost to follow-up. Participants may withdraw from the study at any time and for any reason. Participants will be invited, though not required, to indicate reasons for withdrawal. Those wishing to withdraw from the study will be invited to complete questionnaire assessments via mail rather than attending reassessment/s in person.

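### The post-operative Knee Society Score may be completed by the unblinded treating surgeon, so assessor blinding does not hold for that secondary outcome; its 12-month schedule is also inconsistent

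*Protocol article*

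**What the plan says.** All references are to the protocol article.

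- **Study design:** "The study is a single centre, parallel-arm, double-blinded (participant and assessor), randomised trial with 1:1 random allocation". The Abstract makes the same claim. Neither limits it to particular outcomes.
- **Blinding:** everyone is blinded "with the exception of the treating surgeon/s and theatre staff".
- **Randomisation:** just before induction, "the surgeon will access the allocation code for that participant via an opaque sealed envelope".
- **Surgery:** "One of 12 surgeons will complete each TKR, with training registrars operating under direct supervision".
- **Outcome measures and assessment time points:** "The KSS will be completed by the treating surgeon, training registrar or resident". On the radiographic outcome: "Cement mantle quality will be determined by a surgeon or research assistant trained by a surgeon".
- **Schedule:** the "Knee Society Score" row of Table 1 is marked before randomisation and at 3 months. The outcome list places the KSS in its self-reported group, at 3 and 12 months.

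**The concern.** The one clinical role that must know the allocation is also a named assessor of a listed secondary outcome. A score given by a clinician who knows the arm is open to detection bias, and a larger sample does not remove such bias. Readers who rely on the assessor-blind label would give the KSS comparison more credit than its conduct supports. Filing the KSS under self-reported outcomes makes this worse, because it suggests that blinded participants supply the score.

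The schedule mismatch carries a different risk. If staff work from Table 1, the 12-month KSS is not collected. The Statistical analysis plan section rules out imputation, so that comparison would be lost.

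**Working it through.** The point rests on no figure in the plan, so the check is a comparison of sections.

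**1. Who knows the allocation?** The treating surgeon does, from the envelope (Randomisation) and from the stated exemption (Blinding). Theatre staff do as well. A training registrar does if he or she was in theatre for that patient, which the Surgery section makes possible. A registrar or resident who was not in theatre remains covered by the blinding statement.

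**2. Who assesses which outcome?**

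| Outcome | Assessor in the text | Blinded under the Blinding section? |
|---|---|---|
| Quadriceps strength (primary) | Research assistants | Yes |
| Participant questionnaires | Participant, with research assistant help if needed | Yes |
| KSS, before randomisation | Surgeon, registrar or resident | Not at issue: no allocation yet |
| KSS, after surgery | Treating surgeon, registrar or resident | No for the treating surgeon; depends on theatre presence for the others |
| Cement mantle, 12 months | A surgeon, or a trained research assistant | Yes unless the reader was the operator or in theatre; not stated |

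Only the post-operative KSS row contradicts the Blinding section outright.

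**3. Is there an own-patient exclusion elsewhere?** Yes. The section on adverse events and safety monitoring keeps a surgeon out of the final causality decision for his or her own patient. No matching rule is given for the KSS or the cement mantle.

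**4. How large could the bias be?** Let p be the share of post-operative KSS scored by someone who knows the arm, taken as equal in both arms, and b the difference between arms in how that knowledge shifts the score. The bias in the group difference is p × b, which ranges from 0 (p = 0) to b (p = 1). Sample size does not enter. The documents give neither p nor b, so no number follows.

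**5. Schedule.** In Table 1 the OKS, WOMAC and EQ-5D-5L are marked at both 3 and 12 months; among these four instruments only the KSS lacks the 12-month mark. The Sample size section aims for 45 per group, so 2 × 45 = 90 participants is the most that could lack a 12-month KSS.

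**6. Timing.** Recruitment was expected to start in October 2014 and last 4 years, so to October 2018. Adding 3 months gives January 2019, and adding 12 months gives October 2019. The article is dated 6 December 2018. If recruitment ran to plan and surgery followed soon after enrolment, most 3-month KSS were already scored by then, while some 12-month visits were still to come.

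**The case against.** The strongest reply is that the consequence is narrow. Strength is measured by blinded research assistants with a dynamometer, and pain, function and quality of life are also covered by questionnaires that blinded participants complete. The KSS is one secondary instrument among several. This stands, and it limits how much weight the point can carry.

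The reply is also right on four stronger readings that a reader might infer:

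- **That the cement mantle wording contradicts the blinding claim.** It does not. The text says a surgeon, not the treating surgeon, and a reader outside theatre is blinded under the Blinding section. Assignment of readers may be set out in the full protocol. What remains is a request to state the exclusion.
- **That every registrar who scores the KSS is unblinded.** The text does not say that the scoring registrar is the one who operated.
- **That rater bias can be expressed as a fraction of 0.65 SD.** That effect size was set for quadriceps strength. No expected effect is given for the KSS or the cement mantle, so the ratio would mean nothing for them.
- **That the surgeons hold known preferences.** The Background calls tourniquet use debated and reports usage of 37–93%. It does not describe the views of these 12 surgeons.

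The reply does not remove the core. Nothing in the article reconciles the treating surgeon's exemption from blinding with the same surgeon's role as KSS assessor. Nor is this detail left to a fuller document, since the article states both facts itself.

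**Conclusion.** The point holds for the post-operative KSS: as written, assessor blinding is not in place for that outcome whenever the treating surgeon, or a registrar who was in theatre, does the scoring. It does not reach the primary outcome, the participant-completed questionnaires or the baseline KSS. The cement mantle is a matter for clarification. The 12-month KSS mismatch and the self-reported label are separate inconsistencies that stand on the text alone.

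The size of any bias is unknown, because it depends on how often the operating team scored and on how knowledge of the arm shifted the score. The remark that many 3-month scores already exist assumes that recruitment kept to its stated dates. This should be corrected, but it does not threaten the main comparison.

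**What to change.** 1. **Remaining post-operative KSS:** have them completed by a registrar, resident or trained research assistant who was not in theatre for that patient. The article already names all of these roles.
2. **Cement mantle:** have de-identified films read by someone who did not operate on that patient. This can be done after the event.
3. **KSS already scored:** identify the rater where that was recorded and run a sensitivity analysis without scores given by the operating team. Who scored was settled after randomisation, so also report the number removed in each arm. Where the rater cannot be identified, limit the assessor-blind claim to the outcomes for which it is true.
4. **Schedule and label:** reconcile Table 1 with the outcome list on the 12-month KSS, and list the KSS as clinician-completed.

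The cost is some clinic rostering, preparation of the films and a change of wording. The small downside is that the operating surgeon does not score his or her own patient.
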